### Statistical analysis

For the primary objective, the study will assess the differential impact that the ACT intervention has on the primary outcome of retention. For this measure, ACT will test the difference in the percentage of study participants completing scheduled clinic visits under the hypothesis that the IG’s percentages will exceed CG percentages from baseline to 12 months (“short-term” retention) and to 24 months (“long-term” retention) following transfer to adult care. An initial test of proportions will be conducted at each time period to compare these percentages using a one-way test, and exact *p* values will be calculated using a permutation distribution. Additionally, a Poisson regression model with a time offset will be explored, which will allow for the development of a model to compare rates between the control and intervention arms while accounting for events (i.e., retention) per unit time, which allows time to vary for each subject as well as allowing the inclusion of potential covariates (for example, age, and time since HIV diagnosis).

Similarly, for secondary objective 1, the study will assess the differential impact that the intervention has on viral suppression. For this measure, ACT will test the difference in the percentage of study participants achieving viral suppression, under the hypothesis that the IG percentages will exceed CG percentages at each time period. The strategy in this analysis is similar to that of the primary objective: a one-way test of proportions will be conducted initially, followed by a Poisson count model to account for potential covariates of interest in addition to a temporal component.

For secondary objective 2, the study will assess whether the ACT intervention leads to improvements in the social, emotional, and psychological wellbeing of study participants; improvements in their self-efficacy; or changes in their health locus of control (HLC) from an external to an internal locus of control. Additionally, ACT aims to understanding the potential of psychologically based intervening variables to influence important study outcomes (i.e., increased retention rates and suppressed viral load). To examine important temporal changes in psychological factors, mean changes will be calculated for HLC, FSSQ, MHC-SF, and SRBBS scores from the transfer baseline to 12 and 24 months post transfer. Additionally, between-group comparisons will be made using repeated-measures analysis of variance (ANOVA). Owing to multiple tests among the same subjects, an approximate type 1 error of .05 will be maintained either directly through the use of a technique designed to accommodate repeated-measures designs (e.g., RM-ANOVA), or through the use of post-hoc adjustment of *p* values (e.g., Bonferroni’s method).

Simultaneously, ACT will examine direct and indirect contribution of psychosocial factors on viral-load suppression and retention of study participants in both study arms through multiple mediation model analyses as recommended by Preacher and Hayes [45]. Mediation analyses are particularly useful in randomized control trials as they attempt to capture the effects or processes that occur after randomization. As noted by Preacher and Hayes, the multiple mediation model is preferred over the traditional simple mediation model [45]. Additional mediator/moderator models will also be explored in order to investigate the potential direct and indirect impacts of other ACT intervention components; these will include the use of peer-led support groups during the pre- and post-transfer period, and the relative impact of case management support on retention rates and viral-load measures.

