### Site selection and randomization

Study sites were selected from among secondary- and tertiary-level PEPFAR-supported healthcare facilities with at least 12 months’ experience in providing comprehensive HIV care and treatment services. Eligible sites were further expected to meet the following criteria:At least 20 ALHIV enrolled in care as of 31 July 2016Separate pediatric and adult HIV care teams and clinicsAt least one dedicated physician and one dedicated nurse for each pediatric and adult HIV clinic

All sites were assessed using a standardized tool to determine whether they met the selection criteria.

Our desire was to meet the suggestions of the Consolidated Standards of Reporting Trials (CONSORT) “extension for cluster designs” checklist in our randomization procedure. To that end, we provide details here of both sequence generation and allocation [29]. Twelve healthcare facilities were selected and randomized 1:1 to the intervention and control arms (Fig. 2). These 12 study sites were pair-matched by geographic location and level of care and then randomly assigned to the intervention group (IG) or to the control group (CG). Particular attention was paid to remove bias of group assignment by concealment at the individual participant level. The randomization of facilities was carried out using scripting language in R (v. 3.3.2) by the project statistician [30]. We first created a random number between 1000 and 10,000 and used the result to seed the group assignment so that the results would be reproducible. Based on the pair-matched locations and level of care, we used the “sample” function to determine which member of each matched facility pair would be assigned to each of CG and IG. Of note, age at transfer for each study site was considered in order to include sites that transferred at 15 years as well as 18 years, according to the results of our survey [14]. All enrolled study participants receiving care at each study site will follow the procedures of their respective randomization arms described below.

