### Sample size estimation

The design requires two arms (control = direct transfer without transition period or OSG and intervention = graduated transition with OSG). Six geopolitical zones are included in the design, with two sites (one replicate per arm) located in each zone. The factors considered for the sample size estimate are: at least 80% power, assuming 20% effect size, a confidence level of 95%, a correlation among repeated measures of 0.3, and an intra-class correlation within clusters of 0.05. Further, we assume equal numbers of clusters between CG and IG, and clusters within those conditions to be of equal size. Based on these assumptions, a baseline number of 15 participants per site was needed. This was, however, adjusted for several assumed losses. Based on knowledge of healthcare in this area and among target participants, the following participant loss estimates were made: healthcare transfers out of study sites at 5%, participant moving out of study area at 5%, deaths during the study at 7%, and study withdrawal/dropout at 5%. This results in a total of 22% dropouts, requiring an additional three participants (15 × 0.22) for a total of 18 participants per site. Additionally, we anticipate a 30% rate for declining to participate. Hence, we will need to approach an additional five ALHIV (18 × 0.3) for a total of 23 ALHIV currently enrolled as taking ART at study initiation to ensure that the requirement of 18 participants per site is met. Therefore, for two arms across six zones, we have a recruitment goal of 276 ALHIV (23 × 2 × 6) with a desired final sample size of 216 ALHIV (18 × 2 × 6) consented to participate. Sample size estimation was performed using G*Power (v. 3.1.9.1, Universität Düsseldorf, Germany) and Sampsize (v 0.6, P. Glaziou, ampsize.sourceforge.net) with appropriate adjustments for cluster randomization [44].

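### The retention test as worded compares participants' percentages and does not name the permuted unit, although facilities were randomised in six matched pairs

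*Protocol article*

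**What the plan says.** The Protocol article, Site selection and randomization, makes the facility the unit of allocation: "Twelve healthcare facilities were selected and randomized 1:1 to the intervention and control arms". The allocation was restricted: "These 12 study sites were pair-matched by geographic location and level of care and then randomly assigned". Sample size estimation recognises the clustering. It lists "an intra-class correlation within clusters of 0.05" among its assumptions and states that the calculation was adjusted for cluster randomisation.

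Statistical analysis then defines the primary comparison in terms of participants: "ACT will test the difference in the percentage of study participants completing scheduled clinic visits". The method is given as "An initial test of proportions will be conducted at each time period to compare these percentages using a one-way test", and the sentence ends by saying that exact p "values will be calculated using a permutation distribution". It does not say whether participants or facilities are permuted. A Poisson model is to be explored afterwards, and the covariates offered as examples (age, time since diagnosis) belong to the participant. Viral suppression follows the same strategy. Psychosocial scores are compared by repeated-measures ANOVA, where the only dependence discussed is that between repeated tests on the same subject. Facility, pair, random effects and cluster-robust errors are not mentioned for any outcome.

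**The concern.** Adolescents at one facility share staff, procedures and a routine transfer age, so their outcomes are correlated. Formative consultations says that the standard of care varies widely between facilities. A test that treats participants as independent understates the variance of the difference between arms. Permuting participants does not cure this, because they were not randomised. The allocations that could have occurred are the 2^6 = 64 ways of assigning the arms within the six pairs.

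At stake is the false-positive rate for retention at 12 and at 24 months and for viral suppression. With six facilities per arm, chance differences between facilities could be taken for an effect of the intervention.

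**Working it through.** **The plan's own figure.** Sample size estimation gives 15 participants per site before losses. A repeated-measures ANOVA (between-group factor, f = 0.2, correlation 0.3, alpha 0.05, power 80%) with three measurements needs N = 108. Multiplying by the design effect 1 + (15 - 1) × 0.05 = 1.70 gives 183.6, and 183.6 / 12 = 15.3 per site. Reading the 20% effect size as f = 0.2 and taking three measurements are assumptions, so the match is not unique. It fits the statement that clustering was allowed for in the sample size. The type I error results below do not depend on it.

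**Inputs.** ICC 0.05, 15 per site before losses and 18 enrolled, six facilities per arm (all from the article). Assumed: one-sided 5%, reading the one-way test as one-sided and taking the level from the 95% confidence in the sample size section; a common retention rate of 60-85% under the null.

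**Participant-level z test, whole ICC between facilities within a pair.** The variance is inflated by D = 1 + (m - 1) × ICC, and the true size is P(Z > 1.645 / √D).
- m = 15: D = 1.70; 1.645 / 1.304 = 1.262; size 10.4%.
- m = 18: D = 1.85; 1.645 / 1.360 = 1.209; size 11.3%.

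**Half of the ICC shared within pairs (assumed).** The shared part cancels in the difference, so D falls by m × 0.05 × 0.5.
- m = 15: D = 1.70 - 0.375 = 1.325; size 7.6%.
- m = 18: D = 1.85 - 0.45 = 1.40; size 8.2%.

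**Simulation** (beta-binomial facilities, six pairs, no effect, 15-18 per site, ICC 0.05, one-sided 5%):

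| Test | Whole ICC within pairs | Half shared |
|---|---|---|
| Participants, z test | 10-12% | 8-9% |
| Participants, exact test | 8-10% | 5.5-7% |
| Six pair differences, paired t (5 df) | about 5% | about 5% |
| Facility labels within pairs, 64 arrangements | 2-3% | 2-3% |

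**Sensitivity.** With the whole ICC within pairs, the one-sided z test has size 7.2-8.2% at ICC 0.02 and 14.5-16.2% at ICC 0.10. At two-sided 5% and ICC 0.05 it is 13.3-15.0%. All figures are per time point.

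**Power of the valid tests.** The article gives no control rate, so two pairs of rates are assumed (15 per site, ICC 0.05, no gain from matching, one-sided 5%). The effective number per arm is 90 / 1.70 = 52.9.

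| Rates | Cluster-adjusted z | Paired t, 5 df | 64 arrangements |
|---|---|---|---|
| 60% vs 80% | 73% | 63% | 51% |
| 70% vs 90% | 83% | 74% | 62% |

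**The case against.** The strongest objection is that the permutation clause may already mean the right thing. If facility labels are permuted within pairs, the test is valid, with a simulated size of 2-3%. This stands as a limit on the claim. A reader might infer that the type I error is simply double the nominal level. The article does not support that as a fact: the unit is unnamed, a z test is not the exact test described, and matching on location and level of care may remove some of the variation between facilities. Against this, the sentence sets up a comparison of participants' percentages, and nothing in the section mentions permuting facilities.

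A second objection is that a condensed article may leave random effects and robust errors to an analysis plan that is not shown. The initial test and the open-ended list of covariates fit that view. This carries weight for the Poisson and psychosocial models. It carries less for the primary test, whose method is stated and, on its natural reading, conflicts with the allocation.

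A reader might also infer that confidence intervals would be too narrow. The article specifies no interval for retention or viral suppression, so there is nothing to correct.

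**Conclusion.** The point holds in conditional form. As worded, the primary analysis leaves out the clustering and pairing that the allocation and the sample size recognise, and it leaves the permuted unit open. If participants are the unit, a nominal one-sided 5% exact test has a true size between about 5.5% (half of the ICC shared within pairs) and about 10% (none shared). A z test would have about 8% to 12%. These ranges rest on the article's ICC of 0.05, on 15-18 participants per site and on an assumed one-sided 5% level. Under either reading of the permutation clause the text needs changing, because the choice decides whether the primary p value is valid.

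**What to change.** State one primary analysis at the level of randomisation: the mean of the six within-pair differences in facility retention proportions, tested by a paired t test with 5 df, at 12 and at 24 months. If an exact p value is kept, say that facility labels are permuted within the six pairs (64 arrangements). State the significance level and whether the test is one- or two-sided. Apply the same principle to viral suppression, and include site and pair terms in the Poisson and psychosocial models.

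No new data are needed, but the change is more than wording, because power falls. Under the assumptions above it is about 63% or 74% for the paired t test and 51% or 62% for the 64-arrangement test, against the planned 80%. The power figure in Sample size estimation should be restated for the chosen analysis, with the assumed control rate given. The exact test is also coarse. Its smallest p value is 1/64 = 0.016 one-sided, or 2/64 = 0.031 two-sided. The next two-sided step is 4/64 = 0.063, so a two-sided 5% exact test could reject only at the most extreme arrangement.

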### Data collection

After obtaining informed consent and/or assent, research assistants will collect sociodemographic and medical history information onto enrollment forms by face-to-face interview with study participants and/or their caregivers. Four psychosocial health questionnaires (described below) will also be completed at enrollment by study participants. Completion of the four questionnaires will be repeated at 12, 18, 24, and 36 months after enrollment, coinciding with the transfer time point, and 6, 12, and 24 months post transfer, respectively (Table 1). Blood viral-load sampling will be performed on the same schedule, and the results of all viral-load tests will be reported to clinic providers and filed in participants’ medical charts for use in HIV management. Per national treatment guidelines, stable patients who have been on HIV treatment for at least 6 months should have at least one viral-load test every year [31]. Clinic visits will also be tracked to measure the primary outcome of retention in care.

**Table 1 Tab1:** Adolescent Coordinated Transition (ACT) study timeline, visits, and procedures

Visit	Timeline	Study visit	Procedure	Intervention group	Control group
Enrollment	0 months	Yes	Enrollment	Yes	Yes
			Readiness assessment	Yes	Yes
			Psychosocial assessment^a^	Yes	Yes
			Viral load	Yes	Yes
Visit 1	3 months	Yes	Type of clinic	Pediatric clinic	Pediatric clinic
			Organized support group	Yes	No
			Readiness assessment	Yes	Yes
Visit 2	6 months	Yes	Type of clinic	Adult clinic	Pediatric clinic
			Organized support group	Yes	No
			Readiness assessment	Yes	Yes
Visit 3	9 months	Yes	Type of clinic	Pediatric clinic	Pediatric clinic
			Organized support group	Yes	No
			Readiness assessment	Yes	Yes
Visit 4	12 months	Yes	Type of clinic	Adult clinic	Pediatric clinic
			Organized support group	Yes	No
			Readiness assessment	Yes	Yes
			Viral load	Yes	Yes
Transfer to adult care					
Visit 5	15 months	No	Type of clinic	Adult clinic	Adult clinic
			Organized support group	Yes	No
Visit 6	18 months	Yes	Type of clinic	Adult clinic	Adult clinic
			Organized support group	Yes	No
			Viral load	Yes	Yes
Visit 7	21 months	No	Type of clinic	Adult clinic	Adult clinic
			Organized support group	Yes	No
Visit 8	24 months	Yes	Readiness assessment	Yes	Yes
			Psychosocial Assessment^a^	Yes	Yes
			Viral load	Yes	Yes
End Visit	36 months	Yes	Type of clinic	Adult clinic	Adult clinic
			Readiness assessment	Yes	Yes
			Psychosocial Assessment^a^	Yes	Yes

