The HLC tool has previously been validated by our research team among Nigerian ALHIV, and the MHC-SF has been validated among South African adolescents and adults [34, 40]. All the aforementioned tools will be administered by trained research assistants to study participants for a total of five times during the 3-year follow-up: at enrollment, transfer, and at 6, 12, and 24 months post transfer (Table 1). Additionally, healthcare transition readiness will be assessed twice (at enrollment and at transfer) using the Transition Readiness Assessment Questionnaire (TRAQ) [41, 42]. In a recent systematic review, the TRAQ was determined to be the best-validated transition tool with robust content and construct validity, as well as internal consistency [43].

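### Repeated-measures ANOVA, the only between-group method named for the wellbeing scores, in its classical form compares only adolescents with every analysed questionnaire, a set that can differ by arm

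*Protocol article*

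**What the plan says.** Under Statistical analysis, secondary objective 2 has two parts. First, "mean changes will be calculated for HLC, FSSQ, MHC-SF, and SRBBS scores from the transfer baseline to 12 and 24 months post transfer". Second, "between-group comparisons will be made using repeated-measures analysis of variance (ANOVA"). Error control follows: "an approximate type 1 error of .05 will be maintained", either through a repeated-measures technique or through adjusted p values. No section names a mixed model, imputation or any other use of incomplete questionnaire records.

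Data collection sets the schedule: "Completion of the four questionnaires will be repeated at 12, 18, 24, and 36 months after enrollment". Outcome measures agrees, with the tools given "for a total of five times during the 3-year follow-up". Table 1, however, lists the psychosocial assessment only at months 0, 24 and 36.

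Sample size estimation adds up transfers out (5%), moves (5%), deaths (7%) and withdrawal or dropout (5%): "This results in a total of 22% dropouts". The losses are not split by arm. Study objectives and hypotheses expects higher retention in the intervention arm. Statistical analysis plans mediation models in which psychosocial factors contribute to retention.

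**The concern.** Classical repeated-measures ANOVA needs a score at every occasion in the model, so one missed questionnaire removes the adolescent. A change from transfer to 12 or 24 months likewise needs both scores.

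Completers-only comparisons are biased when missingness depends on both the arm and the score. This protocol supposes both links: the intervention is meant to improve retention, and wellbeing is thought to influence it. If adolescents with low wellbeing are lost more often, and more are lost in control, the remaining control group looks better than the randomised one and a benefit is understated. Other patterns can push the estimate the other way. The affected result is the between-group comparison for a secondary objective.

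**Working it through.** **Inputs from the protocol article.** Sample size estimation gives a correlation among repeated measures of 0.3, an ICC of 0.05, 15 per site before losses, 18 after, 216 in total and 22% loss. It also gives "at least 80% power, assuming 20% effect size". Statistical analysis gives a type 1 error of 0.05.

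**The plan's own figure.** The number of occasions m and the type of effect size are not stated. Taking f = 0.20 in the between-group repeated-measures ANOVA:

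- Noncentrality = N × f² × m / (1 + (m − 1) × 0.3). With m = 3, 80% power needs N = 108 (noncentrality 108 × 0.04 × 3 / 1.6 = 8.1).
- Design effect = 1 + (15 − 1) × 0.05 = 1.7, and 108 × 1.7 = 183.6, or 15.3 per site against the stated 15 (180).
- m = 2, 4 and 5 give 221, 163 and 153, which do not reproduce 180.
- 15 + 15 × 0.22 = 18.3, taken as 18, and 18 × 12 = 216.

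Three occasions is also the number used by the planned changes (transfer, 12 and 24 months post transfer), so the check uses three.

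**Size of the completer set.** 216 × 0.78 = 168.5, so about 48 of the 216 leave the analysis at the planned loss. If the loss splits 32% control and 12% intervention, completers are 108 × 0.68 = 73 and 108 × 0.88 = 95.

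**Bias check (assumptions).** Large-sample simulation with three occasions, correlation 0.3 and a true effect at the second and third. Dropout occurs before the third and depends on the second score, with log-odds rising 0.5 to 1.0 per SD of lower wellbeing, equally in both arms. The all-observed analysis predicts the missing third score from the first two. Estimated effect at the last visit, true value 0.40 SD:

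| Loss, control / intervention | Completers only | All observed scores |
|---|---|---|
| 22% / 22% | 0.40 | 0.40 |
| 27% / 17% | 0.377 to 0.385 | 0.40 |
| 32% / 12% | 0.355 to 0.372 | 0.40 |

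In the middle of the slope range these are 0.38 and 0.36, or (0.40 − 0.38)/0.40 = 5% and (0.40 − 0.36)/0.40 = 10% too small.

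**Average over occasions.** The group effect averaged over all three occasions suffers more, because the average includes the score that drives dropout. With a true 0.30 SD at the second and third occasions, the true average is 0.60/3 = 0.20 SD. Completers give about 0.18 to 0.16 at 27%/17% and 0.15 to 0.11 at 32%/12%. With no true effect, the averaged difference among completers is −0.03 to −0.05 and −0.05 to −0.09 SD respectively.

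**When the last-visit bias is large.** With log-odds of 1.5 per SD in control against 0.3 in intervention, and loss of 31%/18%, completers give about 0.30 to 0.31, which is 22% to 25% too small. With correlation 0.5 and all five occasions, the same contrast in slopes gives 0.23.

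**When the alternative does not help.** If dropout depends on the unseen third score (27%/17%, same slopes), completers give 0.32 to 0.355 and the all-observed analysis 0.33 to 0.36. Both are biased, with a gap of about 0.01.

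**The case against.** The article nowhere says that incomplete records are deleted. That follows from the classical form of the named method. The full protocol or SAP, not shown here, may add imputation or a likelihood-based model. This stands as a limit on certainty. It does not remove the point, because the article itself commits to a method and any such remedy would have to override that sentence.

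A reader might infer that the comparison is restricted to adolescents who stayed in care. The documents do not support that. Retention is defined by clinic visits, and Table 1 separates these from study visits (visits 5 and 7 are not study visits), so an adolescent can be retained and still miss a questionnaire. Of the 22 points of loss, 17 are transfers out, moves and deaths, which need not follow wellbeing. If only a quarter of the loss is score-driven, the estimate is about 0.39 against a true 0.40.

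A reader might also infer attenuation of about a third. A last-visit estimate of 0.26 against 0.40 (35%) can be produced, but it takes a correlation of 0.5 rather than the stated 0.3, complete records at all five occasions, 34%/21% missing at month 36 and dropout assumed more strongly score-driven in control. No section supports that last assumption. Nor should a large gain in precision be claimed for a mixed model: in simulation much of it comes from constraining the arms to a common baseline mean.

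Finally, the mixed model's advantage in the main check is built in, since dropout there depends on an observed score. That objection is sound, and it is why a sensitivity analysis belongs in the fix.

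**Conclusion.** The point holds as a weakness in a stated method. The plan fixes an analysis that, as classically run, uses a post-randomisation subset, in a trial whose own hypotheses link both arm and wellbeing to being lost.

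The expected size is modest for the last-visit contrast: about 5% to 10% of a 0.40 SD effect under the 27%/17% to 32%/12% splits. The effect averaged over occasions is proportionally more exposed. The bias vanishes if loss is equal and depends on the score in the same way in both arms, or if loss is unrelated to wellbeing. Attenuation of about 25% or more at the last visit needs dropout much more score-driven in control. The arm split, the strength of the link to wellbeing and the use of three occasions are all assumptions. The change should be made because it is cheap and the method better, not because a large bias has been shown.

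**What to change.** Replace repeated-measures ANOVA with a likelihood-based linear mixed model on all observed post-enrolment scores. Include arm, visit, arm × visit and the enrolment score as covariate, with random effects for site and participant, small-sample degrees of freedom, and contrasts at 12 and 24 months post transfer. The site effect and degrees of freedom deal with clustering over 12 sites; the use of all observed scores deals with incomplete records.

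Add a sensitivity analysis in which missing scores are worse than predicted, varied by arm, for dropout that depends on unobserved wellbeing. State how deaths (7% expected) are handled, since the model otherwise implicitly extrapolates scores beyond death. Reconcile the five administrations in the text with the three in Table 1, which omits the transfer assessment that the planned changes start from.

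The cost is a few sentences and slightly more analysis work in standard software, with no new data. The downside is reliance on missing at random in the main analysis. The mediation models use the same scores but are separate analyses, and this change does not repair them.

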**Fig. 3 Fig3:**
[figure not shown]
Adolescent Coordinated Transition (ACT) transitioning model showing the 12-month pre-transfer period (adapted from Maturo et al. [19])

Alternating pediatric-adult visits during the 12-month transition period that allows both adult and pediatric clinicians and the transitioning adolescent to address difficulties related to transition and adapt to the termination of the pediatric provider-patient relationship. Transition period clinic visits will be staggered as a Pediatric-Adult-Pediatric-Adult (PAPA) model with a target of four visits in totalA monthly peer-led organized support group (OSG) facilitated by trained young adults living with HIV and guided by a standardized six-module curriculum covering HIV Basics, Treatment and adherence, Support networks, Adolescent rights, Living positively, and Member choice. The OSG curriculum will address topics that will enhance the adolescent’s knowledge of HIV disease and how to self-manage their medical care. Overall, the OSG targets factors that may impact the patient’s transition readiness and psychosocial health measures. ALHIV will have the opportunity to contribute to curriculum content as their OSGs evolve and mature. The OSG will be initiated at enrollment and continued through the 12-month transition period, but to assess potential impact after transfer, it will be extended to the end of the follow-up period at 24 months post transferA case management team consisting of a physician, a nurse, and a trained patient advocate. Patient advocates already exist in these clinics and are usually HIV-infected adults who are selected based on exemplary treatment adherence and clinic attendance. The patient advocate will accompany study participants to all four PAPA clinic visits and will support the peer facilitator to lead the OSG

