In the intervention arm, ALHIV will be transitioned from pediatric to adult care over a period of 1 year. Participants will be enrolled when they are approximately 1 year younger than the routine age of transfer at each study facility (either 15 or 18 years of age). During the 12-month pre-transfer period, ALHIV will be scheduled for clinic visits per the PAPA model. Patient advocates will accompany adolescents to each PAPA clinic visit. In addition, ALHIV receiving care at intervention sites will be encouraged to attend monthly OSG meetings. OSG meetings will be scheduled with routine clinic visits and at adolescent-friendly times to minimize logistical problems and to increase attendance and sustainability. Each OSG will include up to 25 participants.

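### The component models cannot isolate case management or the post-transfer support group, and using post-transfer group attendance as an exposure for retention biases that association upward

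*Protocol article*

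**What the plan says.** The article describes a two-arm design: "Twelve healthcare facilities were selected and randomized 1:1 to the intervention and control arms". Sample size estimation defines the arms as "control = direct transfer without transition period or OSG and intervention = graduated transition with OSG".

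Description of the ACT intervention lists three components: alternating pediatric and adult visits, a monthly support group, and a case management team. They overlap in delivery: "The patient advocate will accompany study participants to all four PAPA clinic visits and will support the peer facilitator to lead the OSG". The same section continues the group to 24 months after transfer and gives assessment of its effect after transfer as the reason. Table 1 shows no organized group for control at any visit where the group is listed.

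On attendance, the section says that "ALHIV receiving care at intervention sites will be encouraged to attend monthly OSG meetings", and that "OSG meetings will be scheduled with routine clinic visits and at adolescent-friendly times to minimize logistical problems". Clinic visits are every 3 months.

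Outcome measures defines retention by counts of clinic visits within 12 and 24 months after transfer. Data collection lists group attendance and the functioning of case management teams among the implementation measures.

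Statistical analysis then states: "Additional mediator/moderator models will also be explored in order to investigate the potential direct and indirect impacts of other ACT intervention components". The components named are "the use of peer-led support groups during the pre- and post-transfer period, and the relative impact of case management support on retention rates"; viral load is also named as an outcome.

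**The concern.** There are two separate problems.

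**Identification.** All three components arrive together with arm. A model that claims the relative impact of one of them needs variation in that component which is not also variation in arm or in the others. Randomization supplies none. The reason given for extending the group also cannot be met, because no site delivers the package without the extension.

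**Timing.** Group use after transfer is named as a component to be related to retention after transfer. Exposure and outcome then accumulate over the same months, and an adolescent who stops coming to the clinic is likely to attend fewer sessions because of having left. The association would look like a benefit of the group even if there were none.

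At stake is how the component results are read. The article hopes to inform transition guidelines and stresses that new programs should need little extra funding, so a reader may well ask which component to keep. It does not say that component estimates will decide this.

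**Working it through.** **1. What the design identifies.** There are 12 facilities, 6 per arm, and one randomized indicator.

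| Component | Intervention sites | Control sites | Variation left |
|---|---|---|---|
| Alternating visits | all 6 | none | individual attendance, fidelity of delivery |
| Support group, before transfer | all 6 | none | individual attendance |
| Support group, after transfer | all 6 | none | individual attendance |
| Case management | all 6 | none | functioning of the team: 6 site-level values |

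Three components share one indicator, so randomization identifies none of their separate effects. What varies within the intervention arm is not randomized. For case management it amounts to six site-level values.

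**2. How closely the group is tied to the clinic.** Meetings are monthly and visits 3-monthly, so at most about 1 meeting in 3 can fall on a routine visit. Two cases bracket this:
- Full coupling: all 3 meetings in a quarter require the adolescent to be in care.
- One-in-three coupling: 1 of the 3 requires it; the other 2 can be attended regardless.

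**3. Loss rates.**
- From the article's Background, 16.1% lost after a mean of 28 months. Assuming a constant rate, the quarterly loss is 1 − (1 − 0.161)^(3/28) = 1.86%, and the 24-month loss is 1 − (1 − 0.0186)^8 = 14.0%.
- Assumed alternative, about 5% per quarter: 1/(1 + e^3) = 4.74%, and 1 − (1 − 0.0474)^8 = 32.2% at 24 months.

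**4. Null simulation over 8 post-transfer quarters.** The group has no effect on retention. The chance of attending each available session is 1/(1 + e^−0.4) = 60% (assumed). Dropout is permanent, which simplifies the visit-based definition. Adolescents above the median number of post-transfer sessions are compared with the rest.

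| Loss rate | Coupling | 24-month retention, high attenders | The rest | Spurious gap |
|---|---|---|---|---|
| 16.1% over 28 months | one in three | 96% | 79% | 17 points |
| 16.1% over 28 months | full | 99% | 77% | 23 points |
| about 5% per quarter | one in three | 89% | 55% | 34 points |
| about 5% per quarter | full | 97% | 44% | 53 points |

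**5. Pre-transfer sessions as exposure, same null, about 5% per quarter.** If adolescents do not differ in their general tendency to attend, retention is 68% in both groups, a gap of 0. If that tendency varies (SD 1 on the logit scale, affecting both sessions and dropout), it is 80% vs 48%. So the earlier window removes the built-in overlap but not confounding by general adherence.

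**6. Check with a visit-based outcome at 12 months.** Inputs: 90 intervention participants (15 × 6 sites), visits at months 3, 6, 9 and 12, and retention as two visits at least 6 months apart. Assumptions: visit attendance 1/(1 + e^−0.85) = 70% for the average adolescent, 50% group attendance when available, no clustering, 4,000 runs, two-sided 0.05 test. The ranges run from SD 0 to SD 1 in visit propensity.

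| Dependence of meetings on visits | Spurious gap | False positives |
|---|---|---|
| none | 0.00 | 5% |
| visit-month meetings only (4 of 12) | 0.13 to 0.20 | 29% to 53% |
| every counted meeting | 0.25 to 0.37 | 82% to 98% |

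**The case against.** **The models are only explored.** The article fixes no exposure definition, lag or adjustment, and such detail normally belongs in an analysis plan that is not shown. This stands in part. The comparison of attenders above and below the median is an illustration, not the planned analysis, and a lagged analysis could avoid much of the overlap. But the article itself names post-transfer group use as a component to be related to retention, and the relative impact of case management as a target. No later choice of coding creates a contrast that the design lacks.

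**The coupling may be weak.** The scheduling sentence sits in a paragraph about the pre-transfer year, so applying it after transfer is an inference, and nothing says that an adolescent out of care is barred from the group. This stands, which is why one-in-three coupling is shown. It reduces the bias without removing it.

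**A reader might infer that every component estimate is circular.** The documents do not support that. Pre-transfer attendance precedes the outcome window, and viral load is not defined by visits; both are confounded by general adherence, which is a different fault. For case management the fault is aliasing with arm.

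**A reader might take 53 points as the size of the bias.** That figure needs full coupling and a loss rate well above the article's own.

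**A reader might infer that the trial's main results are compromised.** They are not. The component models enter neither the arm comparisons nor the sample size.

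**Conclusion.** The concern holds in two parts. First, the design identifies no separate component effect. Case management is aliased with arm apart from non-randomized differences in how six teams function, and the post-transfer extension has no comparator. This follows from the design alone and needs no assumption. Second, relating post-transfer group attendance to retention over the same months biases the association upward when the true effect is zero. The size is about 17 to 23 points at the article's own loss figure and 34 to 53 points at an assumed loss of about 5% per quarter, the lower figure in each range being for one-in-three coupling. These sizes rest on constant loss, permanent dropout, 60% session attendance and a crude median split. The direction does not change as long as leaving care lowers attendance.

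Severity is minor: the models are exploratory, and the primary and secondary comparisons between arms are unaffected.

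**What to change.** In Statistical analysis:
- Remove the claim to estimate the relative impact of case management. Report the functioning of the teams descriptively, by site.
- Do not use concurrent post-transfer group attendance as an exposure for retention. Use group sessions and alternating visits attended in months 0-12, within the intervention arm, with post-transfer retention as the outcome.
- Label all component analyses, including those for viral load, non-randomized and hypothesis-generating, and name general adherence as the likely confounder.

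In Description of the ACT intervention, replace the stated reason for the extension. Say that the 24-month comparison of arms estimates the effect of the whole package with the group still running, not the impact of continuing the group after transfer.

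The cost is wording only, since attendance is already among the implementation measures to be collected. What is given up is a set of component claims that the design cannot support.
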